#### Discharge

The patient may be discharged once vital functions are both normal and stable, and pain is manageable (with or without oral analgesics). Patients in the intervention arm (i.e., PPS) are recommended to stay overnight due to the novel procedure, whereas patients in the endoscopic arm undergo ERCP as a day-case procedure, which is standard protocol in all centers in the Netherlands. Serum liver functions and hemoglobin are routinely checked before discharge; however, normalization of bilirubin is not required prior to discharge. The timing of discharge is determined at the discretion of the treating physician.

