### Primary and secondary endpoints

The primary endpoint of this study is the proportion of patients with major complications within 90 days after randomization. Major complications are defined as any complication leading to prolonged hospital stay of more than 72 h; readmission to a hospital; any invasive reintervention, and/or death, within 90 days after randomization. Major complications include drainage-related complications (Table 1) and complications that do not appear to be drainage-related.

Secondary outcomes include primary and secondary technical success of stent placement at the initial drainage procedure, the number of reinterventions, admission days after drainage, patient-reported quality of life, bile cultures at initial drainage, and primary clinically successful drainage. Other secondary outcomes were the proportion of patients that started with palliative systemic treatment, 90-day mortality, and OS. Primary technical success was defined as successful passage of the stricture and stent placement without leaving an external drain during the initial drainage procedure. Secondary technical success was defined as successful passage of the stricture and stent placement during a second attempt 4–7 days after an unsuccessful initial procedure. Primary clinically successful drainage was defined as a bilirubin 50 µmol/L (> 2.8 mg/dL) or a reduction in bilirubin level of at least 50% within 14 days after the first drainage procedure.

**Table 1 Tab1:** Definitions of severe drainage-related complications

Complication	Criteria
Cholangitis	Elevation in temperature ≥ 38,5 °C and Leukocytes ≥ 10 *10^9^/L, thought to have a biliary cause and requiring invasive intervention, without concomitant evidence of acute cholecystitis.
Acute cholecystitis	Radiologic evidence of cholecystitis, elevation in temperature more than 38.5 °C and Leukocytes ≥ 10 *10^9^/L, requiring emergency cholecystectomy or percutaneous drainage.
Persistent jaundice	Persistent elevated bilirubin levels after primary technically and clinically successful drainage had initially been obtained, without signs of cholangitis or cholecystitis, requiring a reintervention.
Acute pancreatitis	Two or more of the following criteria be met for the diagnosis of acute pancreatitis: abdominal pain suggestive of pancreatitis, serum amylase or lipase level greater than three times the upper normal value, or characteristic imaging findings.

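### Unlimited readmission rule plus different planned stays by arm lets a short first-night complication count after ERCP but not after PPS

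*Protocol article*

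**What the plan says.** Under Primary and secondary endpoints, a major complication is defined by its consequence within 90 days of randomization. The first route is "any complication leading to prolonged hospital stay of more than 72 h". The others are "readmission to a hospital; any invasive reintervention, and/or death". The stay route has a 72 h threshold. The readmission route has no minimum length or severity.

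Under Discharge, the planned stay differs by arm. A night in hospital is advised, but not required, after PPS. The control arm is planned without one: "whereas patients in the endoscopic arm undergo ERCP as a day-case procedure". The same section leaves the final decision open in both arms: "The timing of discharge is determined at the discretion of the treating physician".

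The endpoint section then says: "Major complications include drainage-related complications (Table 1) and complications that do not appear to be drainage-related". Table 1 is headed as listing severe complications. Its rows for cholangitis, cholecystitis, persistent jaundice and biliary leak each require an intervention, and haemorrhage requires transfusion or reintervention. The pancreatitis row asks only for a diagnosis: "Two or more of the following criteria be met for the diagnosis of acute pancreatitis".

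**The concern.** The two consequences that depend on hospital use are not on the same scale, and the arm decides which one applies on the first night. An ERCP patient who is already home can be treated in hospital only by being readmitted, which is an event at once. A PPS patient with the same problem is still in bed, so the index stay is extended, and that is an event only past 72 h. The classification then follows discharge policy as well as the patient's course, and the direction favours the arm the trial hopes to show superior. A positive primary result would be open to that criticism.

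Table 1 raises a different question. If its diagnoses count in their own right, a mild pancreatitis that changes nothing for the patient is a major complication, which does not fit the table's heading or its other rows.

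**Working it through.** **1. The plan's own figure.** Inputs from Sample size calculation: 50% versus 25%, 90% power, two-sided 5%, 1:1 allocation. With unpooled variance, n per arm = (1.960 + 1.282)² × (0.50×0.50 + 0.25×0.75) / 0.25² = 73.55, so 74 per arm and 148 in total. Adding an O'Brien-Fleming-type look at 60% (assumed, as the boundary is not stated) multiplies this by 1.008, giving 148.3. The planned 148 reproduces. The point concerns how events are counted, not the sample size.

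**2. The rules applied to the same complication.** The clock times are illustrative: procedure at hour 0, ERCP discharge at hour 6, PPS discharge at hour 24, no reintervention, 72 h read as total stay.

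| Onset | Duration of care | ERCP | PPS |
|---|---|---|---|
| hour 4 | 36 h | index stay to hour 40: no event | index stay to hour 40: no event |
| hour 12 | 36 h | readmission: **event** | index stay to hour 48: **no event** |
| hour 12 | 72 h | readmission: event | index stay to hour 84: event |
| hour 36 | 36 h | readmission: event | readmission: event |

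Only the second row differs by arm. The asymmetry is therefore confined to short complications that start between day-case discharge and about the next morning.

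**3. What such an asymmetry could do.** The article gives no frequency for these events, so the excess is an assumption. Set the true risk equal in both arms at 30-45%, add a net excess to ERCP only, and compute exact binomial probabilities that a pooled z test exceeds 1.96 in favour of PPS, with 74 per arm and no interim look:

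| Net ERCP-only excess | Chance of a significant result favouring PPS |
|---|---|
| 0 points | 2.5-2.9% |
| 3 points (about 2 of 74 patients) | about 6% |
| 5 points (about 4 of 74) | 9-10% |
| 10 points (about 7 of 74) | about 25% |

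These excesses are net of patients who would have a primary event anyway. If instead x% of all patients have such an event, independently of other events, the net addition is x(1 − p). At p = 0.40 and x = 5 it is 5 × 0.60 = 3.0 points. On that basis x = 3, 5 and 10 give about 4.5%, 6-7% and 11-14.5% over the same range of p.

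**4. What removing such events does to power.** If the 50% control rate includes them, power at 74 per arm against 25% is Φ[(p₁ − 0.25)/√((p₁(1 − p₁) + 0.1875)/74) − 1.96]. This gives 0.85 at p₁ = 0.48, 0.74 at 0.45 and 0.505 at 0.40, against 0.90 at 0.50.

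**5. Table 1.** The pancreatitis row reads the same for both arms. The sentence linking the table to the endpoint has two readings: a Table 1 diagnosis is a major complication by itself, or it is one only if it leads to one of the four consequences. On the first reading, mild pancreatitis counts without a consequence, and so does haemorrhage treated by transfusion alone.

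**The case against.** The case against has several parts.

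- **The window is small.** The overnight stay is only recommended and discharge is left to the physician in both arms. An ERCP complication noticed before discharge and settled within 72 h is not counted, and a PPS patient who returns after the first night is. The hours of the planned PPS stay also run towards the 72 h limit, a small effect in the other direction. All of this stands. It limits the size of the problem but does not remove it.
- **Each strategy is compared as delivered.** The article describes day-case ERCP as standard in Dutch centers, an unplanned return matters to patients, and admission days are a secondary outcome. This is a good reason to leave the primary endpoint alone. It does not show how much of a difference comes from the counting rule.
- **Mild pancreatitis might be taken as further bias towards PPS.** A reader might infer this from its absence in the 67 pilot PPS patients. The documents do not support it: the criterion is identical in both arms, so more cases after ERCP would reflect a difference in procedural risk, not in ascertainment. Counting Table 1 rows automatically would also let in transfusion-only haemorrhage. Haemorrhage occurred in three of 67 pilot PPS patients, although the article says all pilot complications were resolved with reinterventions.
- **The false-positive figures might be read as estimates for this trial.** They are not. They show what follows from an assumed excess.

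**Conclusion.** The point holds in a narrow form. The endpoint definition and the discharge arrangements, taken together, make the counting of a short first-night complication depend on the randomized arm, in the direction of PPS, and the article states no rule that equalises this. It does not follow that early mild complications in general count after ERCP and never after PPS.

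The net bias cannot be derived from the documents. Under equal true risk of 30-45%, a net ERCP-only excess of as little as 3 points would roughly double the one-directional error, from about 2.5-3% to about 6%; if 3% is instead the share of all patients affected, independently of other events, it is about 4.5%. These figures ignore the interim look.

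The missing criterion in the pancreatitis row and the unclear status of Table 1 diagnoses are a separate inconsistency in the primary endpoint, common to both arms.

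**What to change.** Keep the primary endpoint. Before the interim analysis, prespecify a key sensitivity analysis that applies one rule to both arms: a return to hospital within a fixed early window, for example 48 h after the procedure, is treated as part of the index stay. It then counts only if total hospital time for that complication exceeds 72 h, or if there is an invasive reintervention or death.

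State also that every Table 1 diagnosis, including pancreatitis and transfusion-only haemorrhage, is a primary event only if it meets one of the four consequences.

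The cost is some extra analysis work, admission and discharge times precise enough to apply the window, and somewhat lower event rates and power in the sensitivity analysis. The loss is small if such events are rare. If they made up 5 or 10 points of the assumed 50% control rate, power would fall to about 74% or 50%, which is a reason not to redefine the primary endpoint itself during the trial.

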### Primary and secondary endpoints

The primary endpoint of this study is the proportion of patients with major complications within 90 days after randomization. Major complications are defined as any complication leading to prolonged hospital stay of more than 72 h; readmission to a hospital; any invasive reintervention, and/or death, within 90 days after randomization. Major complications include drainage-related complications (Table 1) and complications that do not appear to be drainage-related.

Secondary outcomes include primary and secondary technical success of stent placement at the initial drainage procedure, the number of reinterventions, admission days after drainage, patient-reported quality of life, bile cultures at initial drainage, and primary clinically successful drainage. Other secondary outcomes were the proportion of patients that started with palliative systemic treatment, 90-day mortality, and OS. Primary technical success was defined as successful passage of the stricture and stent placement without leaving an external drain during the initial drainage procedure. Secondary technical success was defined as successful passage of the stricture and stent placement during a second attempt 4–7 days after an unsuccessful initial procedure. Primary clinically successful drainage was defined as a bilirubin 50 µmol/L (> 2.8 mg/dL) or a reduction in bilirubin level of at least 50% within 14 days after the first drainage procedure.

**Table 1 Tab1:** Definitions of severe drainage-related complications

Complication	Criteria
Cholangitis	Elevation in temperature ≥ 38,5 °C and Leukocytes ≥ 10 *10^9^/L, thought to have a biliary cause and requiring invasive intervention, without concomitant evidence of acute cholecystitis.
Acute cholecystitis	Radiologic evidence of cholecystitis, elevation in temperature more than 38.5 °C and Leukocytes ≥ 10 *10^9^/L, requiring emergency cholecystectomy or percutaneous drainage.
Persistent jaundice	Persistent elevated bilirubin levels after primary technically and clinically successful drainage had initially been obtained, without signs of cholangitis or cholecystitis, requiring a reintervention.
Acute pancreatitis	Two or more of the following criteria be met for the diagnosis of acute pancreatitis: abdominal pain suggestive of pancreatitis, serum amylase or lipase level greater than three times the upper normal value, or characteristic imaging findings.
Biliary leak	Symptomatic intra-abdominal bile leakage due to bile duct perforation or leakage from the puncture tract documented by any radiographic technique requiring intervention.
Haemorrhage	Clinical evidence of bleeding requiring blood transfusion or reintervention.

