### Trial eligibility

Patients with unresectable MHBO and hyperbilirubinemia > 50 µmol/L (> 2.8 mg/dL) are screened for inclusion. All patients are discussed in a multidisciplinary team in an academic center to confirm ineligibility for both liver resection and liver transplantation. Unresectability can be due to local tumor extension (i.e., locally advanced disease), distant metastases, insufficient future liver remnant (FLR) function due to liver parenchyma disease, and/or poor patient performance. Ineligibility for liver transplantation is based on international guidelines [13]. Written informed consent is obtained. Cytological or histological confirmation of malignancy is recommended. However, study inclusion is also allowed if the multidisciplinary team agrees that the risk of malignancy is very high based on symptoms, imaging, and laboratory values.

Exclusion criteria include a high suspicion of benign disease, for example because of fluctuation or spontaneous decrease in bilirubin levels before the initiation of any treatment or a high IgG4. Previous biliary drainage attempts and clinical signs of cholangitis are other exclusion criteria. Cholangitis is defined as the presence of both fever (i.e., body temperature ≥ 38.5 °C) and leukocytosis (i.e., ≥ 10 × 10^9^/L) without clinical or radiological evidence of acute cholecystitis [14]. Patients who underwent an attempted, but failed ERCP are eligible only when no papillotomy or cannulation was performed.

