#### Follow-up

About 14 days after biliary drainage, serum bilirubin is measure and primary clinically successful drainage is assessed. Patients are recommended to have a consultation with a medical oncologist to discuss palliative systemic treatment. Quality of life is measured before treatment and at two weeks, one month, and three months follow-up using the EORTC QLQ-C30 and BIL21 questionnaires [16, 17]. The EORTC QLQ-C30 assesses quality of life specifically for cancer patients. The BIL21 focuses on symptoms related to patients with biliary tract cancer.

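### The definition of primary clinically successful drainage carries only a greater-than sign, so as printed a patient whose bilirubin does not fall counts as a success

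*Protocol article*

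**What the plan says.** Four places in the protocol article bear on this.

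- **Primary and secondary endpoints, text.** The outcome is listed among the secondary outcomes ("bile cultures at initial drainage, and primary clinically successful drainage"). Its absolute limb reads "Primary clinically successful drainage was defined as a bilirubin 50 µmol/L (> 2.8 mg/dL", with no sign before 50 and a greater-than sign before 2.8. From that sign the sentence runs on into the relative limb: "> 2.8 mg/dL) or a reduction in bilirubin level of at least 50% within 14 days after the first drainage procedure". The two limbs are alternatives, so meeting either one is enough.
- **Trial eligibility.** The entry condition uses the same threshold and the same sign: "Patients with unresectable MHBO and hyperbilirubinemia > 50 µmol/L (> 2.8 mg/dL) are screened for inclusion".
- **Table 1, persistent jaundice.** This complication is recognised only "after primary technically and clinically successful drainage had initially been obtained", so it depends on the definition above.
- **Follow-up.** This section gives the timing but does not restate the rule: "About 14 days after biliary drainage, serum bilirubin is measure and primary clinically successful drainage is assessed".

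Under Statistical analysis, dichotomous outcomes other than the primary are compared between arms by the Chi-squared test. Absolute and relative bilirubin decrease are compared as continuous outcomes by the Mann-Whitney U test.

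**The concern.** A success criterion for drainage should separate patients whose jaundice has cleared from those in whom it has not. The printed criterion borrows the sign that defines jaundice at entry. Because the limbs are joined by an or, a patient who satisfies the wrongly signed limb is a success whatever happens on the other limb.

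At stake is a named secondary outcome that will be tested between arms, and the Table 1 label that depends on it. That label is not a rare one. In the pilot described in the Background, persistent jaundice accounted for 6 of the 12 severe drainage-related complications (9.0% of patients, out of 17.9%).

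**Working it through.** **Inputs.** Let B0 be bilirubin at entry, B14 the value at assessment and T the threshold (50 µmol/L, glossed as 2.8 mg/dL). Entry requires B0 > T (Trial eligibility).

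**Rule as printed, using its only sign.** Success if B14 > T, or (B0 − B14)/B0 ≥ 0.50.

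1. Entry already requires B0 > T. If bilirubin stays the same or rises, B14 ≥ B0 > T, so the patient is a success.
2. Failure requires both B14 ≤ T and B14 > 0.5 × B0. Together these give B0 < 2 × B14 ≤ 2T, that is, an entry value below 100 µmol/L (or 5.6 mg/dL).
3. So the only possible failures are patients who entered below about 100 µmol/L and came down to or below the threshold. A patient who entered at 100 µmol/L or more cannot fail.

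**Rule with the absolute limb turned round.** Success if B14 < T, or (B0 − B14)/B0 ≥ 0.50.

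Illustrative cases, with T = 50 µmol/L:

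| B0 → B14 (µmol/L) | Fall | As printed | Sign turned round |
|---|---|---|---|
| 300 → 280 | 20/300 = 7% | success | failure |
| 80 → 60 | 20/80 = 25% | success | failure |
| 60 → 60 | 0% | success | failure |
| 70 → 45 | 25/70 = 36% | failure | success |
| 300 → 150 | 150/300 = 50% | success | success |
| 300 → 40 | 260/300 = 87% | success | success |
| 80 → 40 | 40/80 = 50% | success | success |

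The two rules agree only where the 50% reduction is met, and at a value of exactly 50 µmol/L. Elsewhere they give opposite answers.

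**Could a sign simply have been lost?** A less-than sign survives elsewhere in the article (the significance threshold under Statistical analysis). Even if one had dropped out before 50, the printed greater-than sign on the mg/dL figure would contradict it.

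**Units.** The article does not give a conversion factor. Its own pairs imply two different ones: 50/2.8 = 17.9 µmol/L per mg/dL here and under Trial eligibility, and 250/15 = 16.7 under Antibiotics. Across that range, 50 µmol/L corresponds to 2.8 to 3.0 mg/dL. With an assumed factor of 17.1:

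- 50/17.1 = 2.92 mg/dL, which rounds to 2.9 and not 2.8;
- 2.8 × 17.1 = 47.9 µmol/L;
- 250/17.1 = 14.6 mg/dL, which rounds to the printed 15.

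The mismatch at the threshold is about 4% (2.92/2.8 = 1.04). It matters only for values between 47.9 and 50 µmol/L, which lie below one printed threshold and above the other.

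**Reach into the primary endpoint.** A major complication is any complication that leads to a stay beyond 72 h, readmission, an invasive reintervention or death, whether or not it appears related to drainage. Table 1 persistent jaundice already requires a reintervention. A patient with an invasive reintervention for jaundice is therefore captured by the general criterion, whichever label Table 1 assigns. The sample size calculation uses complication rates of 50% and 25%, the power, the significance level and one interim analysis. The drainage-success definition is not among its inputs.

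**The case against.** The strongest reply is that this is a drafting slip with only one sensible reading. The term being defined is successful drainage, the other limb is a fall in bilirubin, and 50 µmol/L is the entry threshold for jaundice, so success must mean coming below it. No analyst is likely to code an unchanged bilirubin as a success. The underlying values are collected at about two weeks, so the binary outcome can be derived correctly from the same data. The continuous comparison of bilirubin decrease does not use this definition at all.

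Much of that stands. The intended direction is clear, and nothing suggests that the trial meant to count jaundice as success. But the article states the definition, and states it wrongly, so this is not a detail left to a fuller document. The direction can be inferred. Which of the two unequal thresholds applies cannot.

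Three stronger readings are tempting, and the article does not support them.

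- **That the error corrupts the primary endpoint through persistent jaundice.** The general criteria count an invasive reintervention whatever its label.
- **That the trial loses its bilirubin comparison.** The continuous analyses remain.
- **That a day-15 sample can never show success, because one section says within 14 days and another says about 14 days.** Visit windows, like the baseline value for the 50% reduction, are commonly left to the full protocol or analysis plan. The difference in wording is worth aligning but is not an error of consequence.

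**Conclusion.** The definition is wrong as written and should be corrected. Taken at its only printed sign, it inverts a named secondary outcome: patients with no fall in bilirubin succeed, and the only failures are patients who reached the threshold or below from an entry value under about 100 µmol/L. The classification of persistent jaundice in Table 1 is affected because it uses the same term. Under the printed rule, a technically stented patient whose bilirubin never fell satisfies the clinical-success precondition; with the sign turned round, that patient does not.

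The damage stops there. Primary-endpoint status is essentially unaffected, and the sample size does not depend on the definition. The unit mismatch is small and separate from the sign error.

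The conclusion about the sign follows from the text alone. The unit figures rest on the assumed factor of 17.1. How many patients would be misclassified cannot be stated, because the article gives no distribution of bilirubin at entry or at two weeks.

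**What to change.** In Primary and secondary endpoints, define primary clinically successful drainage as a bilirubin below 50 µmol/L (< 50 µmol/L, < 2.9 mg/dL), or a reduction of at least 50%, with the less-than sign printed in both units. The sponsor should confirm which unit governs and make the µmol/L and mg/dL figures agree here and under Trial eligibility. The 2.9 assumes that µmol/L governs and a factor of 17.1.

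As a minor tidy-up, use the same timing wording in this definition and under Follow-up.

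The correction should be recorded before results by arm could influence it. Randomization began in August 2023, and interim results by arm go to the DSMB. Any rule already programmed for this outcome or for Table 1 persistent jaundice should be checked against the corrected sentence.

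The cost is one sentence of definition and one unit figure. No new data are needed, and neither the sample size nor the primary analysis changes.
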